### Primary outcome

The primary outcome measure of this RCT is the urinary concentration of the carcinogen biomarker of tobacco exposure, NNAL.

### Secondary outcomes

The secondary outcome measure will be urine cotinine concentration. Markers of oxidative stress (Glutithione and 8-Isoprostanes) are additional secondary outcome measures. Glutathione will be measured via blood sample analysis. 8-Isoprostanes will be measured via both urine sample and exhaled breath condensate analyses.

### Sample size

RCT power is based on the important biomarker of toxicant exposure, NNAL concentration in urine. Unfortunately, there are no data that reveal the NNK exposure in ECIG users, as that study has not yet been performed. However, we do have data showing how NNAL concentration in novel tobacco product users compares to own brand cigarette use [49]. Using these data, power analysis revealed 100 completers per condition would provide an 80 % power to detect an effect size of 0.28 pmol/ml (SD = 0.6 pmol/ml) on NNAL. We aim to enroll 130 participants per condition anticipating a 20 % attrition rate.

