### Randomization, allocation concealment, and sequence generation

The four conditions are a cigarette substitute that does not produce aerosol, 0 mg/ml nicotine content ECIG (placebo), 8 mg/ml nicotine content ECIG (low), and 36 mg/ml nicotine content ECIG (high). Blocked randomization is accomplished with a 1:1:1:1 ratio of condition assignments at each participating institution with a goal of 260 randomized per site (*N* = 260 for VCU and PSU; *N* = 520 total). The assignment codes are made from separate randomization lists created in advance by the statistician for each site stratum. The randomization lists are stored in a secure, password protected drive and are shared only with unblinded staff. Once a participant has been confirmed eligible for randomization, a computer procedure will assign the participant to the next condition on the list automatically.

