### Statistical analysis

The analysis plan is based on the primary objective of determining the extent to which ECIG nicotine concentration influences NNK exposure as indexed by urinary NNAL concentration. We will first examine baseline characteristics including demographics and smoking history across study interventions to identify any baseline imbalances after randomization. Discrete variables will be summarized by frequencies and percentages and compared using Chi-squared test or Fisher’s exact test. Continuous covariates will be summarized by mean, standard deviation, median and range, and compared by one-way ANOVA. Skewed continuous variables will be log-transformed or square root transformed as appropriate. We expect groups to be balanced for important baseline characteristics due to randomization. A secondary analysis will be completed adjusting for age, gender, and race, along with any other covariates that differ across research interventions at baseline with a p-value less than 0.20. P-values less than 0.05 will be considered statistically significant with the exception of analysis of our primary analysis, where p-values less than 0.008 will be considered significant after a Bonferroni multiple comparisons adjustment. Our primary endpoint, urine NNAL concentration, will be summarized by study intervention and time and analyzed using linear regression, and we will adjust the Type I error rate to account for 6 pairwise comparisons at each time point. We will compare each ECIG group to the cigarette substitute and then each ECIG group to the other. An analogous approach will be used to analyze our secondary endpoints. The primary analysis of our secondary endpoints will use linear regression. Secondary analyses will consist of an adjusted analysis and a repeated measures analysis using a linear mixed model. All analysis will be completed using SAS (v.9.4) under the expertise of a senior biostatistician.

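### The stated 80% power for NNAL does not reproduce at the plan's own 0.008 threshold: with two-sided tests it is about 73-74% with 100 completers per condition and about 75-76% with 104

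*Protocol article*

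**What the plan says.** The protocol article, Sample size, bases the trial's power on urinary NNAL, the primary outcome. It claims that "100 completers per condition would provide an 80 % power to detect an effect size of 0.28 pmol/ml"; the SD assumed there is 0.6 pmol/ml. On dropout it adds: "We aim to enroll 130 participants per condition anticipating a 20 % attrition rate". No alpha, sidedness or test is attached to the 80%.

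The Statistical analysis section gives the decision rule for that endpoint. The model for NNAL is a linear regression, with results given by arm and time. On multiplicity the article says: "we will adjust the Type I error rate to account for 6 pairwise comparisons at each time point". The resulting cut-off for this primary analysis is that "p-values less than 0.008 will be considered significant after a Bonferroni multiple comparisons adjustment". The contrasts are each ECIG arm against the cigarette substitute, and the ECIG arms against one another. Allocation is equal across the four arms (Randomization section: "Blocked randomization is accomplished with a 1:1:1:1 ratio of condition assignments at each participating institution"), so every pairwise contrast compares two groups of the same planned size.

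**The concern.** A power figure has meaning only for a particular test at a particular significance level. The article prints a difference, an SD, a group size and a power in one section, and a strict per-comparison threshold in another. If the 80% was worked out for a more lenient threshold or a different test, the planned pairwise analysis has less power than readers are told.

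The chance of missing a true 0.28 pmol/ml difference in a given pairwise comparison is at stake. The article implies 20%. NNAL is the only primary outcome and the hypothesis concerns concentration-related differences, so individual pairwise results will be interpreted.

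**Working it through.** **Inputs.** Difference 0.28 pmol/ml, SD 0.6 pmol/ml and 100 completers per condition (Sample size); threshold 0.008, from 0.05/6 = 0.00833 (Statistical analysis); 1:1 allocation within each pair (Randomization). Two-sided testing is an assumption.

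**Formula.** The standard error of a pairwise difference is SD × √(2/n), and the noncentrality is the difference divided by that standard error. Normal-approximation power is Φ(noncentrality − z at 1 − α/2). The exact version uses the noncentral t, with 198 df for two arms or 396 df if the error is pooled over four arms.

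- Standard error: 0.6 × √(2/100) = 0.0849.
- Noncentrality: 0.28 / 0.0849 = 3.30. The standardised difference is 0.28/0.6 = 0.467.

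**Trying to reproduce the stated 80%, n = 100.**

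| Test | Normal | Noncentral t (198 df) |
|---|---|---|
| Two-sided 0.05 | 91.0% | 90.7% |
| Two-sided 0.05/3 | 81.8% | 81.1% |
| Two-sided 0.0125 | 78.9% | 78.1% |
| Two-sided 0.05/6 | 74.6% | 73.6% |
| **Two-sided 0.008 (plan's threshold)** | **74.1%** | **73.2%** |
| One-sided 0.008 | 81.4% | 80.7% |

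With pooled four-arm error (396 df), two-sided 0.008 gives 73.7%. A four-group omnibus F test at 0.05 gives 79.5% if two means lie 0.28 apart and the other two midway between them. The two-sided alpha that gives exactly 80% is about 0.014 (normal) to 0.015 (t), and the article states no such level.

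Normal check at the plan's threshold: z at 0.996 is 2.652, so Φ(3.300 − 2.652) = Φ(0.648) = 74.1%.

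**Completers implied by enrolment.** 130 × 0.8 = 104 per condition. Two-sided power at 0.008 is then 76.2% (normal), 75.3% (t, two arms) or 75.8% (t, pooled).

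**Difference detectable with 80% power at two-sided 0.008.** By the normal formula with n = 100, (2.652 + 0.842) × 0.0849 = 0.296; the t version gives 0.299 pmol/ml. With n = 104 the t version gives 0.293.

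**Completers needed for 80% power at 0.28 and 0.008.** 2 × (2.652 + 0.842)² × 0.6² / 0.28² = 112.1, so 113 per condition; the t version gives 114. This only shows the size of the gap and is not a recommendation.

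**The case against.** **Sidedness.** The article does not say that the tests are two-sided, and its toxicant hypothesis is directional (decreases relative to the substitute). One-sided 0.008 would give about 81% and would bear out the printed figure. This limits certainty. It does not remove the mismatch, because no section declares one-sided tests and regression p-values are two-sided by default.

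**Rounding of the SD.** The SD is printed to one decimal. At two-sided 0.008 with 100 completers, an SD of 0.56 gives 80.3% and 0.55 gives 82.0%, but 0.649 gives 64.5%. Rounding works in both directions and does not support 80% in particular.

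**Size.** With 104 completers the gap is only 4 to 5 points, and the detectable difference moves from 0.28 to about 0.29. The article itself says that no NNK exposure data exist for ECIG users, so 0.28 is borrowed from another product class. The shift is small beside that uncertainty. This objection stands, and it is why the point is a correction to the reporting and no threat to the trial.

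**Stronger readings.** A reader might infer that the sponsor corrected for three comparisons by mistake, since 0.05/3 gives about 81%. The documents do not support that inference: 0.0125, one-sided 0.008 and one form of the omnibus F test also come within two points of 80%, so the origin of the figure cannot be identified. A reader might also infer that the primary conclusion is unsafe or that enrolment must rise. Neither follows. The type I error rule, endpoint and allocation are untouched, and a completed null comparison is judged from its confidence interval, not from planned power.

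**Conclusion.** The power statement is wrong as written when set against the article's own decision rule. At the declared 0.008 threshold the type II error for a 0.28 pmol/ml difference is about 26-27% with 100 completers per condition and about 24-25% with 104, against the 20% implied. The shortfall is 6 to 7 points at 100 completers and 4 to 5 at 104.

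The conclusion rests on two-sided pairwise tests, which is the one assumption not in the text, and on the SD of 0.6 as printed. A separate analysis plan could explain where the 80% came from. It could not make 80% the power of the two-sided test at 0.008 with the printed inputs. This should be fixed, but it does not endanger the trial.

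**What to change.** Restate the power sentence in the Sample size section with the alpha, sidedness and test, so that it matches the Statistical analysis section. For example:

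*With a two-sided 0.008 threshold for each of 6 pairwise comparisons and SD 0.6 pmol/ml, power to detect 0.28 pmol/ml is about 73% with 100 completers per condition (about 75% with 104); 80% power corresponds to a difference of about 0.30 pmol/ml (0.29 with 104).*

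If the 80% was derived for another test or for one-sided testing, the article should say so and still give the power of the planned pairwise comparison.

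The cost is one sentence and a slightly less favourable figure. Enrolment, allocation and the significance rule stay as they are. The text should not claim that 80% at 0.28 is recovered by adjusting for baseline NNAL, because that depends on a baseline correlation that the article does not give.

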### Withdrawal criteria

There are numerous criteria in place for withdrawal consideration. Non-compliance with study procedures (e.g., consistently missing visits, not maintaining their daily dairies, unable to use their study product for a period of more than two weeks not by choice) are grounds for PI-consultation and withdrawal. Furthermore, participants will also be withdrawn from the study if they present with serious clinical adverse events, pregnancy, recurring illness, a new illness that could adversely interact with study participation, or worsening substance abuse. Any hospitalization at any time during participation is also grounds for study withdrawal. Hospitalizations will be self-reported by the participant and will be reviewed by the site PI and medical professional to determine whether continued participation in the study is appropriate (e.g., recovery from a major surgery, worsening of psychiatric symptoms, etc.). Finally, if a participant is behaving in an inappropriate or threatening manner, admits to dishonesty about eligibility criteria, is participating in other smoking research studies that could affect the primary outcome measures, appears/admits to giving away/selling study products, consistently loses study products etc., then they may be withdrawn from the study at the PI’s discretion.

Participants may also choose to remove themselves from the study by informing the research team in writing at any point during the study. If they choose to remove themselves from the study, they will not receive any further contact from the study site.

If participants are withdrawn from the study for any of the reasons noted above prior to randomization, they will be replaced until a total of 260 participants have been randomized to the study at each study site (VCU and PSU). Reasons for withdrawal will be ascertained from participants who withdraw from the study.

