
### Aim

The specific aims of the RCT are to:*Characterize ECIG influence on toxicants*, *biomarkers, health indicators, and disease risk.* We will measure exposure to the carcinogenic nitrosamine 4-(methylnitrosamino)-1-(3-pyridyl)-1-butanone [NNK; via its metabolite NNAL (4-(methylnitrosamino)-1-(3-pyridyl)-1-butanol) in urine], expired air carbon monoxide (CO), and nicotine (via its metabolite cotinine in urine). We will also measure heart rate and blood pressure, biochemical and hematologic health indices, pulmonary function (via spirometry), and biomarkers of oxidative stress. With respect to toxicant exposure, we hypothesize that, relative to the cigarette substitute condition, we will observe ECIG liquid nicotine concentration-related decreases in urine NNAL and expired air CO concentration.*Determine the tobacco abstinence symptom and adverse event profile associated with real-world ECIG use*. We will use standard measures of nicotine/tobacco abstinence symptoms to characterize the extent to which ECIG-induced suppression of abstinence symptoms is related to nicotine concentration. With respect to other adverse events, we will assess effects likely attributable to inhalation of propylene glycol and nicotine self-administration. We hypothesize more of these propylene glycol-related adverse events with ECIGs relative to the cigarette substitute condition.*Examine the influence of ECIG use on conventional tobacco product use.* We will monitor ECIG and all other tobacco/nicotine product use closely, via daily tobacco use diaries and in-person assessments. Because we are targeting individuals interested in reducing their cigarette intake, we hypothesize that individuals randomized to higher ECIG nicotine concentrations (8 mg/ml or 36 mg/ml) will experience reductions in combustible cigarette use.

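### The withdrawal criteria take randomised participants out of the study, not only off the product, so later NNAL and safety data are lost when they could still be collected

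*Protocol article*

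**What the plan says.** The Withdrawal criteria section of the protocol article lists grounds of differing force.

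- **Mandatory wording.** "participants will also be withdrawn from the study if they present with serious clinical adverse events". The same sentence covers pregnancy, recurring illness, a new illness that could interact badly with participation, and worsening substance abuse.
- **After review.** "Any hospitalization at any time during participation is also grounds for study withdrawal". The site investigator and a medical professional then decide whether the person should continue.
- **After consultation with the investigator.** Non-compliance, with the examples "consistently missing visits, not maintaining their daily dairies" and being "unable to use their study product for a period of more than two weeks not by choice) are grounds for PI-consultation and withdrawal".
- **At the investigator's discretion.** Among others, a participant who gives away or sells products or "consistently loses study products etc., then they may be withdrawn from the study".

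Replacement is limited to people withdrawn "prior to randomization, they will be replaced until a total of 260 participants have been randomized" at each site. For people who remove themselves, the section adds that "they will not receive any further contact from the study site". It does not say what happens to visits and samples when staff withdraw a participant.

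The Aim section gives as its second aim: "Determine the tobacco abstinence symptom and adverse event profile associated with real-world ECIG use".

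**The concern.** Stopping a product and leaving a trial are different events. A participant who can no longer use the product, or should not, can usually still give urine, recall the past week's smoking and report adverse events. If the rule ends participation instead, the data stop for reasons that arise after randomisation and may be related to both product and smoking.

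Two things are at stake. First, a participant with no sample at a time point contributes nothing to that time point's NNAL comparison. If those lost differ from those who stay, and the losses differ between arms, the comparison is biased. Second, people with a serious event or a hospital stay are those whose later course matters most to an adverse-event profile, and observation of them may end at the event.

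**Working it through.** **Step 1. Do the grounds operate after randomisation?** Yes. Under Study visits, product is first handed out at Visit 2, after assignment, so every product-based ground arises after randomisation. Hospitalisation counts at any time. Because replacement covers only earlier withdrawals, later losses are permanent.

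**Step 2. Are data lost?** Study visits places urine collection among the biomeasures at Visits 2, 5, 7 and 10 (weeks 0, 4, 12 and 24). Adverse events, side effects and the 7-day Timeline Follow Back are taken at each visit after consent. Someone out of the study attends no visits. Under Statistical analysis, NNAL is analysed by linear regression with pairwise comparisons at each time point, so a missing sample drops that person from that comparison. Under Sample size, power is counted on completers.

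**Step 3. Could the loss differ by arm?** The e-cigarette arms depend on batteries, chargers and about three cartomizers a day; the substitute arm receives two plastic tubes. The substitute arm is unblinded (Blinding section), so discretionary decisions can be made knowing e-cigarette versus substitute. The three e-cigarette arms share device and supply and are blinded to concentration, so this mechanism bears mainly on the three comparisons with the substitute.

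**Step 4. The plan's own figure.** Inputs: difference 0.28 pmol/ml, SD 0.6, 100 completers per arm, 80% power, 130 enrolled, 20% attrition.

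- Power = Φ(0.28 / (0.6 × √(2/n)) − z).
- At n = 100, the standard error is 0.6 × √(2/100) = 0.0849, and 0.28/0.0849 = 3.30.
- One-sided 0.008 (z = 2.41) gives power 0.81, and two-sided 0.05/3 gives 0.82. Either reproduces the stated 80%.
- Two-sided 0.008 gives 0.74, and two-sided 0.05 gives 0.91.

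The section does not state which alpha was used. That is a separate matter and does not affect this point.

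**Step 5. Cost in power of extra loss** (two-sided 0.008, 130 per arm):

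| Loss | Completers per arm | Power |
|---|---|---|
| 20% (planned) | 104 | 0.76 |
| 30% | 91 | 0.69 |
| 40% | 78 | 0.60 |

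Only the first row is the plan's assumption.

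**Step 6. Selective loss: illustration only.** If a fraction w of one arm is lost, and its mean differs from that of those who stay by g, the observed arm mean moves by w × g. With no such loss in the other arm, the contrast moves by the same amount. The values of w and g are assumed.

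- w = 5%, g = 0.3 (0.5 SD): 0.05 × 0.3 = 0.015 pmol/ml; 0.015/0.28 = 5%.
- w = 10%, g = 0.6 (1 SD): 0.10 × 0.6 = 0.06 pmol/ml; 0.06/0.28 = 21%.
- Wider range, w = 10–30% and g = 0.15–0.6 (0.25–1 SD): 0.10 × 0.15 = 0.015 to 0.30 × 0.6 = 0.18 pmol/ml, or 5–64% of 0.28.

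For scale, 5–10% of 130 is about 7–13 people, and the standard error of a contrast with 104 per arm is 0.6 × √(2/104) = 0.083 pmol/ml.

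**The case against.** A reader might infer that anyone who does not use the product is removed, so that the primary comparison becomes one among adherent participants. The text does not support that. The product ground is inability to use it, expressly not by choice. Voluntary non-use is not listed, so on this ground those participants stay in.

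Other objections have force:

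- Most grounds are not automatic. They pass through consultation, review or discretion; only the sentence on serious events, pregnancy, illness and substance abuse is mandatory.
- Data loss is inferred for staff-withdrawn participants. An end to contact is stated only for those who remove themselves, and a fuller protocol may say more.
- Two batteries and continuing replacement make a two-week involuntary interruption less likely.
- Samples given before withdrawal are not said to be discarded, and a repeated measures mixed model, which can use partial records, is among the secondary analyses.
- The triggering event is still documented, and serious events and drop-out rates are reported to the monitoring board. Only later observation is at risk.
- People withdrawn for missing visits were already supplying little.
- The Discussion's expectation that substitute participants could be more likely to withdraw concerns their own choice, which this fix would not change.
- In the 5–10% illustration, the largest shift (0.06) is below one standard error (0.083), and these losses may fall within the planned 20%.

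These points limit the size of the concern but do not remove it. The section words several grounds as withdrawal from the study, one set is mandatory, and nothing in the article keeps follow-up open. A mixed model cannot supply NNAL values that were never collected.

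**Conclusion.** The point holds as a modest, inexpensive improvement in conduct. The article provides for study-level withdrawal of randomised participants and never separates it from stopping the product. Applied as worded, it loses later NNAL, smoking-recall and adverse-event data that could often still be obtained, and it sits poorly with the second aim.

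This rests on reading withdrawal from the study in its ordinary sense, as an end to study visits. A difference between arms is plausible mainly for e-cigarette versus substitute. The documents give neither the number affected nor how they differ from others, so size and direction are unknown. The 5–21% range, and the wider 5–64%, show only what the assumed values imply. The upper end of the wider range takes 30% loss in one arm, above the 20% planned for all causes. The documents do not support a conclusion that the primary result is invalid or limited to adherent users.

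**What to change.** In the Withdrawal criteria section, leave every existing ground for stopping the study product as it stands and separate it from ending follow-up. State that randomised participants who meet one of these grounds are invited to attend the remaining scheduled visits for urine collection, the Timeline Follow Back and adverse-event assessment, and are analysed in their assigned arm. Follow-up would end only when consent is withdrawn, or when the site judges continued attendance unsafe or inappropriate. The no-contact provision for people who remove themselves stays unchanged.

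Record the date and reason for stopping product separately from the date and reason for leaving the study, by arm, so that selective loss can be seen.

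The cost is protocol and consent wording, plus gift cards and visit time for what should be a small number of participants. The change has to be made in conduct, because analysis cannot recover samples that were not taken.
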